### Sample size calculation

Sample size is calculated according to the study of Arab and colleagues [7]. In clinical practice, multipoint injection and satisfactory diffusion of LA will result in more complete sensory or motor blockade and faster onset times. Therefore, we expected a higher rate of complete sensory blockade using the new TI technique. Based on a pilot study (15 patients), the rate was 66.7% (patients with complete sensory blockade) at 20 min after injection, when patients received a standardized IA-SCB with the DI technique. We hypothesized that the TI technique will be capable of increasing this rate to 90%; with a statistical power of 0.80 and a *α* level of 0.05, the required sample size is calculated to 36 patients per group. A total of 43 patients per group will be required to account non-included patients (15% dropout rate).

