## Methods and analysis

### Trial design

This study is a single-center, randomized, double-blind, parallel-group clinical trial with concealed 1:1 allocation to receive either a DI or TI technique to IA-SCB of patients scheduled for elective upper limb arteriovenous access surgery. The trial will be carried out at the Guangdong Provincial People’s Hospital, Guangzhou, Guangdong, China, and started in July 2021 and the recruiting period will be 18 months. Trial methods and results will be reported according to the Consolidated Standards of Reporting Trials (CONSORT) 2010 guidelines (Fig. 1). The schedule of enrolment and assessments is shown in the Standard Protocol Items: Recommendations for Interventional Trials (Fig. 2).

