### Statistical plan

Statistical analysis will be performed using SPSS version 20 statistical software (SPSS Inc, Chicago, IL). Firstly, an overall descriptive analysis and inferential statistics for all clinical variables in both groups will be performed. Numbers and percentages will be recorded for categorical variables, and mean (SD) and interquartile intervals for continuous variables. For all data, normal distribution will be examined by the Kolmogorov-Smirnov test. The basic information (such as age, BMI, and performance times, etc.) will be analyzed using chi-square tests or Fisher’s exact test or independent *t* test as appropriate. The percentage of patients with a complete sensory blockade at all predetermined time points and onset times will be analyzed using the Mann-Whitney *U* test or independent *t* test. The incidence of diaphragmatic paralysis, surgical anesthesia, and operation-related adverse events will be analyzed using chi-square tests or Fisher’s exact test. A *P* value inferior to 0.05 will be considered statistically significant for all results.

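### The 36 per group reproduces only with a one-sided 5% test; a two-sided test at 0.05 has about 69% power at that size, not the stated 80%

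*Protocol article*

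**What the plan says.** All inputs stand in the Sample size calculation section of the protocol article:

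- Control rate, from a pilot of 15 patients: "the rate was 66.7% (patients with complete sensory blockade) at 20 min after injection".
- Expected rate with triple injection: the authors suppose that "the TI technique will be capable of increasing this rate to 90" per cent.
- Error rates and result: the calculation is made "with a statistical power of 0.80" and an alpha of 0.05, from which "the required sample size is calculated to 36 patients per group".
- Loss: 15% dropout raises 36 to 43 per group, 86 in all.

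The Trial design section describes a "parallel-group clinical trial with concealed 1:1 allocation". The Statistical plan assigns the percentage with complete sensory blockade to a Mann-Whitney U test or an independent t test, and sets one threshold: a P "value inferior to 0.05 will be considered statistically significant for all results". Neither section says whether testing is one-sided or two-sided.

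**The concern.** The paragraph gives every input needed to repeat the calculation, and under a two-sided test at 0.05 the result is well above 36. The stated figure needs a one-sided test that the protocol never declares and that its significance rule does not carry into the analysis.

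This is the only power statement for the only primary outcome. If it is wrong, the trial claims a sensitivity it lacks, and a non-significant result would be judged against an 80% figure that does not apply. The inflation for dropout starts from the same 36, so the shortfall passes into the planned total of 86.

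**Working it through.** **Inputs.** p1 = 0.667, p2 = 0.90, difference d = 0.233, mean rate p̄ = 0.7835, 1:1 allocation, power 0.80 (z = 0.842), alpha 0.05 (z = 1.645 one-sided, 1.960 two-sided). Sidedness is not given, so both were tried.

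Variance term: 0.667 × 0.333 + 0.90 × 0.10 = 0.2221 + 0.0900 = 0.3121. Squared difference: 0.233² = 0.05429.

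**Reproducing the plan's 36.** Unpooled formula, n = (zα + zβ)² × [p1(1 − p1) + p2(1 − p2)] / d²:

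- One-sided: (1.645 + 0.842)² × 0.3121 / 0.05429 = 35.5, rounded up to 36.
- Two-sided: (1.960 + 0.842)² × 0.3121 / 0.05429 = 45.1, rounded up to 46.

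Pooled formula, n = [zα√(2p̄(1 − p̄)) + zβ√(p1(1 − p1) + p2(1 − p2))]² / d², where the two square roots are 0.5825 and 0.5587:

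- One-sided: (1.645 × 0.5825 + 0.842 × 0.5587)² / 0.05429 = 37.6, rounded up to 38.
- Two-sided: (1.960 × 0.5825 + 0.842 × 0.5587)² / 0.05429 = 47.9, rounded up to 48.

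Arcsine formula, n = 2[(zα + zβ)/h]² with h = 2 arcsin√0.90 − 2 arcsin√0.667 = 0.587: 35.9 one-sided, 45.6 two-sided.

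| Method | One-sided 0.05 | Two-sided 0.05 |
|---|---|---|
| Unpooled | 36 | 46 |
| Arcsine | 36 | 46 |
| Pooled | 38 | 48 |
| Pooled, continuity corrected | 46 | 57 (56 if p1 = 2/3) |

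Fisher's exact test, by enumeration, needs about 55 per group two-sided. No two-sided method gives 36.

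**Dropout step.** 36 / 0.85 = 42.4, rounded up to 43. This step is right.

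**Power actually available, two-sided 0.05.** The chi-square and Fisher rows come from summing binomial probabilities over all possible outcomes.

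| Test | 36 per group | 43 per group |
|---|---|---|
| Pearson chi-square, exact enumeration | 69% | 78% |
| Pooled normal approximation | 68% | 76% |
| Fisher's exact test | 59% | 68% |

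The tests that the Statistical plan names do not change this. Applied to a yes/no outcome, the t test and the Mann-Whitney test without continuity correction give 69% at 36 and 78% at 43, the same as chi-square.

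The chance of missing the hypothesised effect with 36 evaluable per group is 100% − 69% = 31%, against the 20% claimed.

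**Size needed to keep 80%.** 48 / 0.85 = 56.5, rounded up to 57 per group, 114 in total, against the planned 86.

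**The case against.** The best counter-argument is that sidedness is never stated. The hypothesis is worded in one direction, since the authors expect triple injection to do better, and on a one-sided 5% reading 36 is right: exact chi-square power is then 79.5%. It is true that two-sided is a reading and not a quotation. But expecting a benefit is common to every superiority trial and does not declare a one-sided test. The single P < 0.05 rule also covers baseline variables, diaphragmatic paralysis and adverse events, where a one-sided test favouring triple injection would make no sense. If a one-sided test was meant, the paragraph still omits the one assumption on which its number depends.

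A second point is that 69% assumes the full 15% loss. The outcome is read 20 minutes after injection, so refusing later follow-up need not remove a patient from the primary analysis, and power could approach 78%. This is fair, and both figures are given here. But the plan itself counts on 36 evaluable, its dropout criteria include departures from the study plan, and 78% is still below 80%.

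Third, the Fisher figures are secondary, because the protocol does not assign that test to the primary outcome. That is correct, and the conclusion does not depend on them.

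Last, the pooled figure of 48 and the exact power figures come from different methods; by exact chi-square enumeration, 46 per group already gives 80.1%. The corrected paragraph should label each figure with its method. The gap from 36 remains on either basis.

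**Conclusion.** The concern holds. With 66.7% against 90%, 1:1 allocation and two-sided alpha 0.05, 36 per group gives about 69% power, some 11 points below the stated 80%, and analysing all 43 per group gives about 78%. The required number before dropout is 46 to 48 by the common formulas, so the plan is 10 to 12 patients per group short of its own target. The conclusion rests on the conventional two-sided reading of the 0.05 threshold and on the protocol's assumed rates. Type I error and the treatment comparison itself are unaffected; what is wrong is the power claim. It must be corrected, because it is the only statement of what this trial can detect on its primary outcome.

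**What to change.** Rewrite the sample size paragraph so that it says:

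- the primary comparison is two-sided at 0.05;
- for 66.7% against 90% with 80% power, the pooled formula requires 48 per group before dropout;
- the planned 86 patients give about 78% power if all 43 per group are analysed and about 69% with 36 per group (exact chi-square power).

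In the Statistical plan, name the Pearson chi-square test without continuity correction as the primary test. The restated power then matches the analysis; Fisher's exact test would lower it to 68% and 59%.

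The test should not be relabelled one-sided now. The Trial status section reports that patients have already been enrolled, so this would relax the criterion after the start.

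The cost is a paragraph of wording and a less favourable stated power, with no new patients. Restoring 80% with 15% loss would instead take 57 per group, 28 more patients in total (114 − 86). That would be a design change, and the Protocol amendments section in principle allows changes only for safety.

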### Statistical plan

Statistical analysis will be performed using SPSS version 20 statistical software (SPSS Inc, Chicago, IL). Firstly, an overall descriptive analysis and inferential statistics for all clinical variables in both groups will be performed. Numbers and percentages will be recorded for categorical variables, and mean (SD) and interquartile intervals for continuous variables. For all data, normal distribution will be examined by the Kolmogorov-Smirnov test. The basic information (such as age, BMI, and performance times, etc.) will be analyzed using chi-square tests or Fisher’s exact test or independent *t* test as appropriate. The percentage of patients with a complete sensory blockade at all predetermined time points and onset times will be analyzed using the Mann-Whitney *U* test or independent *t* test. The incidence of diaphragmatic paralysis, surgical anesthesia, and operation-related adverse events will be analyzed using chi-square tests or Fisher’s exact test. A *P* value inferior to 0.05 will be considered statistically significant for all results.

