Needle techniques for traditional supraclavicular blocks include sub-epineurium injection (e.g., double injection [6]), intracluster injection (e.g., triple [7], targeted intracluster injection [8, 9]), or extra-epineurium injection (e.g., corner pocket injection [10]). Although the total anesthesia-related times vary in those studies, the results have demonstrated that the multiple injection technique is feasible and can achieve faster onset times and higher success rates within 30 min after injection, with no increase in complications [11]. The triple-injection technique described by Arab et al. [7] was designed based on the clusters of the brachial plexus at the level of the first rib, which can be artificially divided into three parts. The percentage of patients with complete sensory blockade was up to 76% in TI vs 56% in single injection for upper limb arteriovenous access surgery at 20 min after injection. However, a cadaver study has reported that even single intracluster injection could lead to a high risk of sub-perineurium injections (up to 24%) in the traditional supraclavicular block, which raised concerns about nerve injury [4]. Fortunately, the 3 separate compartments visualized during the intertruncal approach are naturally occurring along the trajectory of the brachial plexus, in which each trunk is separated not yet blended. Consequently, in this trial, we will compare DI vs TI ultrasound-guided IA-SCB. Based on our initial experience, we hypothesized that the new TI technique will result in a higher percentage of patients with complete sensory blockade in the first 20 min, while avoiding puncture-related adverse events.

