Although our study has many similarities to Arab’s study [7], some important differences are worth noting: (1) The TI is not an intracluster-injection technique, rather than a precise sub-epineurium injection technique (puncture the epineurium of the trunks under real-time ultrasound guidance); (2) compared with the classical approach to supraclavicular block, the new intertruncal approach provides clearer anatomical details, including the 3 trunks and its hyperechoic epineurium layers, which may guide the needle tip to the targeted location without intraneural injection. Furthermore, small nerves arise from the fascicles, and the intracluster-injection technique may result in sub-perineurium injections. The TI technique deposits the LA away from the trunks, even if the needle is advanced within the neurovascular sheath. Therefore, the greatest advantage of this TI technique is that keeping the needle tip outside of the perineurium as far as possible on ultrasound imaging. We also observe the puncture-related variables (paresthesia and procedural-related pain), diaphragmatic paralysis, and neurological deficits to evaluating the safety of this TI technique. Therefore, ultrasound-guided IA-SCB with the TI technique has the potential to be as “all for one” technique of the whole upper extremity similar as selective trunk block [19, 20], which can provide more complete blockade and rapid onset time with low incidence of adverse events.

This study protocol has several limitations. First, this is a single-center study and has all the limitations inherent in that study design. Second, our study will focus on the block dynamic in patients undergoing a same type of surgery, which is insufficient statistical power for rare but serious complications. The prospective or retrospective clinical study with a large sample will be desired in the future for the incidence of nerve injury and pneumothorax. Third, we cannot completely rule out that the skill level of the operators affects the block dynamic and puncture-related complications, even if we chose all experienced ones in this study protocol.

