In conclusion, this trial is the first prospective, randomized, parallel, double-blind study evaluating the block characteristics for DI vs TI technique when used in new IA-SCB in patients undergoing upper limb arteriovenous access surgery. If the TI technique yields better block dynamic, it would bring strong data to promote the TI technique in IA-SCB. It may provide us with an ideal needle technique for optimized risk-benefit and advance the understanding of the optimal site of injection and optimization of the diffusion of LA in IA-SCB.

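### The hypothesis that triple injection avoids puncture-related adverse events has only difference tests behind it, and a non-significant difference test cannot support it

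*Protocol article*

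**What the plan says.** The Introduction of the protocol article states a hypothesis in two parts. TI is to give a "higher percentage of patients with complete sensory blockade in the first 20 min, while avoiding puncture-related adverse events". No tolerable increase or margin is attached to the second part.

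The Discussion returns to safety. It lists two puncture-related variables, paresthesia and procedural pain, and adds "diaphragmatic paralysis, and neurological deficits to evaluating the safety of this TI technique". It concedes "insufficient statistical power for rare but serious complications" and points to nerve injury and pneumothorax as the events that need larger studies. It closes by saying of TI: "It may provide us with an ideal needle technique for optimized risk-benefit".

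Under Statistical plan, categorical variables are summarised as numbers and percentages. The inferential rule is: "The incidence of diaphragmatic paralysis, surgical anesthesia, and operation-related adverse events will be analyzed using chi-square tests or Fisher’s exact test". The threshold is a P "value inferior to 0.05 will be considered statistically significant for all results". Neither a margin nor a confidence interval for the difference between groups is named.

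Under Sample size calculation, the trial is sized "with a statistical power of 0.80 and a" 0.05 significance level for the primary outcome only: 36 evaluable patients per group, raised to 43 for 15% dropout.

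**The concern.** A chi-square or Fisher test takes equality as its null hypothesis. Rejection shows a difference, but non-rejection does not establish equality, and still less that harm has been avoided. The method chosen therefore cannot deliver the second part of the hypothesis. The most favourable result it can return is a failure to reject.

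Whether this matters in practice depends on how large an excess could go unnoticed. The sample size was set by an expected rise in complete block from 66.7% to 90%, which says nothing about adverse events. The admitted limitation covers rare serious complications. It does not cover paresthesia, procedural pain or diaphragmatic paralysis, on which most of the comparative safety information will rest.

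At stake is the wording of the conclusion. A favourable block result together with P>0.05 on adverse events could be written up as a better risk-benefit balance, although the data might still be compatible with a substantial excess under TI.

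**Working it through.** **Inputs from the protocol.** Evaluable n = 36 per group, randomised n = 43 per group, 1:1 allocation, threshold 0.05, tests chi-square or Fisher. Sidedness is not stated; two-sided is assumed for the safety comparisons. The DI rates of paresthesia and diaphragmatic paralysis are not given, so I take a range from 5% to 40%.

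**The plan's own figure.** For 66.7% vs 90%, the unpooled normal formula is n = (z_alpha + z_beta)² × [p1(1−p1) + p2(1−p2)] / (p2−p1)².

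- One-sided 0.05: (1.645 + 0.842)² × (0.2221 + 0.0900) / 0.233² = 35.5, so 36, as stated.
- Two-sided 0.05: the same formula gives 45.1, so 46. The stated 36 therefore matches a one-sided test.
- Dropout: 36 / (1 − 0.15) = 42.4, so 43, as stated.

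No adverse-event rate enters this calculation.

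**Chance of missing a true doubling.** For each pair of rates, I summed the product of the two binomial probabilities over every table with two-sided P≥0.05. Entries are Fisher / uncorrected chi-square.

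| DI → TI (assumed) | n = 36 per group | n = 43 per group |
|---|---|---|
| 5% → 10% | 97% / 87% | 95% / 84% |
| 10% → 20% | 86% / 78% | 83% / 74% |
| 15% → 30% | 76% / 67% | 70% / 60% |
| 20% → 40% | 63% / 53% | 55% / 46% |
| 25% → 50% | 50% / 39% | 39% / 31% |
| 30% → 60% | 36% / 27% | 26% / 19% |
| 40% → 80% | 9% / 5% | 4% / 2% |

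Up to a DI rate of about 15%, a doubling is missed more often than not. At 20% it is close to even, and from about 25-30% it is mostly detected. A tripling is easier to see: 15% → 45% is missed only 12-26% of the time.

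**One possible result.** Take 4/43 (9.3%) with DI and 10/43 (23.3%) with TI, a difference of 14.0 points.

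- Fisher P = 0.14.
- Uncorrected chi-square: z = 0.1395 / √(0.1628 × 0.8372 × 2/43) = 1.75, P = 0.08.
- Wilson limits: DI 3.7% to 21.6%, TI 13.2% to 37.7%.
- Newcombe lower limit: 0.1395 − √[(0.2326 − 0.1315)² + (0.2160 − 0.0930)²] = −0.020.
- Newcombe upper limit: 0.1395 + √[(0.3774 − 0.2326)² + (0.0930 − 0.0368)²] = +0.295.

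TI has two and a half times the events, neither permitted test is significant, and an excess of 29 points is not excluded.

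**Precision when the true rates are equal.** The approximate half-width of the 95% interval is 1.96 × √[2p(1−p)/n]. Over n = 43 to 36 this is 9-10 points at p = 5%, 13-14 at 10%, 17-19 at 20% and 19-21 at 30%.

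**Zero events in a group.** The upper 97.5% bound is 1 − 0.025^(1/n): 8.2% for 0/43 and 9.7% for 0/36.

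**Procedural pain.** This is a 0-10 score. For a true difference of 0.5 SD (assumed), a two-sided t test misses it 37% of the time at 43 per group and 45% at 36.

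**The case against.** The strongest reply is that the protocol contains no rule by which P>0.05 is declared safety. A reader might infer one from the hypothesis and the closing remarks, but the text does not support that: the risk-benefit sentence is tentative and follows a condition on block dynamics, and a low incidence of adverse events is described as a potential of TI. This stands. What remains is narrower: the hypothesis includes avoidance, and the only inference provided cannot support it.

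A reader might also conclude that the trial would usually miss a doubling or more of any of these events. That cannot be said without a DI rate. It fails from about 25-30% upward, and sooner for larger increases. If diaphragmatic paralysis is common with DI, a doubling would probably be seen. More extreme tables can also turn on which test is used: 4/43 vs 12/43 gives Fisher P = 0.0501 but chi-square P = 0.027. The example above was chosen because both tests agree.

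Nor is diaphragmatic paralysis clearly part of the hypothesis. The Discussion lists it apart from the puncture-related variables, so it belongs to the wider safety evaluation only.

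Finally, confidence intervals are often left to an analysis plan, which is not shown here, and group counts let any reader compute them. That would answer a complaint about a missing interval. It does not answer a mismatch between a stated hypothesis and the stated method. Group counts, the adverse-event form and the monitoring committee help to oversee safety, but they do not set how the comparison is to be interpreted.

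**Conclusion.** The point holds in a limited form. The avoidance part of the hypothesis, and the wider safety evaluation in the Discussion, rest on counts and difference tests at P<0.05 in a trial sized for efficacy. A non-significant result would not support avoidance whatever the baseline rate: even at a DI rate where a doubling is usually detected, only an interval shows which excess has been excluded.

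The practical size is conditional. With assumed DI rates of 5-15%, a true doubling goes undetected 60-97% of the time at 36 to 43 per group (74-86% for 10% vs 20%). At 20% the figure is 46-63%. These ranges span both permitted tests and both group sizes, two-sided. The primary comparison is not affected. The change is worth making because it governs what may be concluded about safety.

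**What to change.** In the Statistical plan, keep the tests if wanted, and add:

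- the TI minus DI risk difference with a Newcombe 95% confidence interval for puncture-related paresthesia and for diaphragmatic paralysis;
- the mean difference with 95% confidence interval for the 0-10 procedural pain score;
- exact upper bounds per group for outcomes with no events;
- a sentence that P>0.05 will not be taken as evidence that TI avoids, or does not increase, adverse events, and that the safety statement will rest on the upper confidence limits.

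In the Introduction, reword the avoidance clause as an aim to estimate the difference in puncture-related events. In the Discussion, extend the power limitation to paresthesia and, if it proves uncommon, diaphragmatic paralysis, and make the risk-benefit remark depend on the upper limits.

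The cost is a few sentences and a few intervals from data already being collected, with no extra patients. The downside is a more cautious safety statement.
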